### Outcome measures

The study period is 2 weeks. Patients in both groups will be evaluated at baseline and week 2, the healthy individuals only at enrollment. All outcomes will be measured by evaluators who will be blinded to group allocation. All evaluators will receive the same training on these evaluations.

### Primary outcomes

Blood oxygen level-dependent functional magnetic resonance imaging (BOLD-fMRI) indirectly evaluates neuronal activity by monitoring changes in blood oxygenation (10). Amplitude of low frequency fluctuation (ALFF) and regional homogeneity (ReHo) are common evaluation indicators (11). ALFF represents the spontaneous activity of neurons, and its derivative, fraction amplitude of low frequency fluctuation (fALFF), can better remove noise signals such as heartbeat and respiration, and is more sensitive and precise. ReHo responds to intervoxel activity synchronization by calculating the consistency of voxels over time series. The two indicators have better repeatability and clear physiological significance. Functional connectivity (FC) reflects functional integration between regions.

Voxel-based morphometry (VBM) is a structural MRI quantitative analysis technique in which gray matter volume or gray matter density can be obtained by calculating the gray matter.

Diffusion tensor imaging (DTI) technique traces fiber bundle alignment and identifies structural changes in white matter fibers (12), and fractional anisotropy (FA) is the most commonly used measure reflecting the integrity of white matter fiber bundles (13).

Arterial spin labeling (ASL) is a magnetic resonance perfusion imaging technique that can be used to detect cerebral blood perfusion (14). As an important indicator, cerebral blood floot (CBF) can reflect cerebral blood flow perfusion (15).

### Secondary outcomes

National Institutes of Health Stroke Scale (NIHSS), modified Rankin Scale (mRS), Fugl–Meyer Assessment (FMA), Modified Barthel Index (MBI) and EuroQol Five Dimensions Questionnaire (EQ-5D) will be assessed before and after 2 weeks of treatment as secondary outcomes.

FMA (16) is widely used in motor function assessment which can reflect the level of limb function recovery in patients with post-stroke disability. The scale focuses on limb joint flexibility and muscle strength, including 66 points for the upper limbs and 34 points for the lower limbs, with a total score of 100 as normal. Currently, the Spanish, Russian, and German versions of the FMA are used for clinical assessment with high sensitivity and validity. Consistency of motor scores in patients with post-stroke dysfunction due to harmonization of kinematic measurement tools (17).

NIHSS (18) can quickly measure the severity of stroke and is recommended as a valid tool for stroke in the emergency department. It consists of 15 items with a total score of 42, the higher the score, the more severe it is. Numerous data demonstrate its reliability, validity, ability to predict stroke outcomes, and strong correlation with infarct foci on imaging. The NIHSS only provides a cursory assessment of the patient’s impairment and does not provide detailed information.

The mRS (19) is highly reproducible and has convergence with other disability scales. Compared to the Barthel Index, mRS is reliable in that it predicts outcomes more accurately. The World Health Organization (WHO) (20) recommends the mRS as an indicator of stroke outcome. The mRS is categorized into 7 grades covering physical function and ability to live, allowing for assessment of patient prognosis.

The MBI is a 100-point scale that assesses 10 essential abilities of patients in their daily lives, and is one of the more widely used and researched methods of assessing activities of daily living. EQ-5D has five dimensions to measure health, including mobility, self-care, daily activities, pain/discomfort, and anxiety/depression. EQ-5D-5L (21) scale which each dimension is divided into five levels, increasing the reliability, validity, and sensitivity of the measurement tool.

### Data acquisition

Data will be acquired by a Siemens Skyra 3.0 T MRI scanner (Siemens Healthineers) equipped with a 32-channel head coil. For BOLD-fMRI images, we used an echo-planar imaging (EPI) sequence (repetition time (TR) = 2,000 ms, echo time (TE) = 30 ms, flip angle = 90°, matrix = 64 × 64, field of view (FOV) = 220 mm × 220 mm, resolution = 3.4 × 3.4 × 3.0 mm^3^, gap = 0.99 mm, 240 time points, 37 interleaved axial slices). The structural image of the whole brain will be acquired for each participant using the T1 sequence (TR = 2,000 ms, TE = 1.97 ms, FOV = 256 mm × 256 mm, matrix = 192 × 192, voxel size = 1 × 1 × 1 mm^3^). White matter fiber bundle structure will be acquired from the DTI sequence (voxel size = 2 × 2 × 2 mm^3^, TE = 75 ms, TR = 8,200 ms, 70 slices, matrix = 110 × 110, FOV = 220 × 220 mm^2^, b = 0,1,000 s/mm^2^, and 64 diffusion directions). The cerebral perfusion imaging will be acquired by ASL sequence (TR = 4,000 ms, TE = 16.18 ms, matrix = 64 × 64, FOV = 220 × 220 mm^2^, voxel size = 3.4 × 3.4 × 3.0 mm^3^ TI1/TI = 700/1990 ms). Subjects’ heads will be immobilized by cushioned supports, and they will wear earplugs to protect against MRI gradient noise throughout the experiment.

For the observation steps, we will communicate with the patient in advance about the length of the scanning, so that the patient will not feel anxious if the time is too long. The subject’s ears will be plugged with cotton balls. When the patient is ready, the patient’s entire brain will be scanned. During resting-state scanning, patients will be instructed to relax, close their eyes, remain still, and avoid thinking activities as much as possible.

### Adverse events and safety monitoring

Adverse events will be assessed and managed by designated personnel within 24 h. Patients may voluntarily inform their physician of the presence of an AE at the time of the visit and during follow-up, or they may be screened for the presence of an AE by physical examination, laboratory tests, or other methods of assessment. These data will be evaluated by two investigators and documented on the CRF, including those taken by the instructing practitioner for acupuncture treatments after an AE occurs, such as discontinuance of acupuncture, resumption of acupuncture after a pause, reduction in the frequency or adjustment of the treatment regimen, continuation of acupuncture, and other interventions taken. If the adverse event is accompanied by medication or other treatment, it should be documented at the same time. Subjects may withdraw from the trial at their own discretion, or the physician may decide whether the patient should continue or terminate the study by evaluation.

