### Inclusion criteria

The inclusion criteria are as follows:

1. Patients group:Meets the above diagnostic criteria;First-ever clinical CIS occurred ≤2 weeks, the number of times ≤ 1;40–70 years old, right-handed;Unilateral basal ganglia infarction and the area of infarction is 3.0 ~ 5.0 cm in diameter at the largest level, with motor dysfunction and manual muscle testing showing muscle strength grades 1 to 4;No severe cognitive impairment and also mini-mental state examination (MMSE) with a score of 17 or above.Provided written informed consent to participate.

2. Healthy people groupAge and sex were matched with the patient group, right-handed;Subjects are in good health and free of organic and significant functional diseases;No previous family history of the mental and nervous system;No stimulant drugs have been taken in the past 2 months;Provided written informed consent to participate.

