### Acupuncture group

Acupoints of XNKQ acupuncture included bilateral PC6, DU26, and affected side SP6. Patients will be in the supine position. Acupoints will be sterilized with 75% alcohol before acupuncture. The first acupuncture point to be needled will be PC6, then the needle body will be rotated to stimulate the acupoints with a speed of 40-60/min and a rotation angle of more than 180°. The second will be DU26, the needle body will be rotated 360° and fixed to the skin, and moved to stimulate the acupoint until the eye is moist or weeping. Finally, SP6 will be stimulated until the leg twitches 3 times.

Depending on each patient’s tolerance level, the therapist adjusts the acupuncture strength until the patient achieves “deqi” without significant pain. Leave the needle in place for 30 min per treatment. Acupuncture 6 times per week for 2 weeks for a total of 12 times.

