### Non-acupuncture group

In the non-acupuncture group, patients will receive the same basic treatments as the acupuncture group except for acupuncture.

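### Adverse events are collected by voluntary report or optional screening while one arm has 12 extra sessions, so by-arm counts may reflect unequal opportunity to report

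*Protocol article*

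**What the plan says.** The section Adverse events and safety monitoring names two routes by which an event comes to notice. The first is unsolicited: "Patients may voluntarily inform their physician of the presence of an AE at the time of the visit and during follow-up". The second follows in the same sentence: "or they may be screened for the presence of an AE by physical examination, laboratory tests, or other methods of assessment". Both are worded as possibilities, and no day or common set of questions is attached to either. Events found are then evaluated by two investigators and entered on the case report form. The text does not distinguish the arms.

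Contact differs by design. Under Acupuncture group: "Acupuncture 6 times per week for 2 weeks for a total of 12 times". Under Non-acupuncture group: "patients will receive the same basic treatments as the acupuncture group except for acupuncture". No sham or attention visit is described. Under Outcome measures: "Patients in both groups will be evaluated at baseline and week 2". Table 1 marks adverse events only in the 2-week treatment column. The abstract says that adverse events will be observed and recorded as the safety assessment. The statistical section names no comparison of them between arms.

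**The concern.** Unsolicited reporting depends on meeting someone to report to. Patients in the acupuncture arm meet a therapist on 12 occasions that have no counterpart in the control arm, so under the plan as written the opportunity to report follows allocation. A mild or passing event in the first week is likely to be mentioned at the next session in one arm. In the other it may have to be remembered until week 2, unless a ward contact happens to pick it up.

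The population makes spontaneous recall a weak instrument. Patients are within 2 weeks of a stroke and may enter with "mini-mental state examination (MMSE) with a score of 17 or above". That criterion applies to both arms and creates no imbalance alone. It does lower the yield of each contact, so the number of contacts matters more.

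At stake is how the safety results can be read. The randomised control arm is the only reference inside the trial for separating events of the stroke and its usual care from events of needling. If adverse events are listed by arm, readers will compare the columns. They could not then tell an excess under acupuncture from more chances to report, or a low control count from under-recording.

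**Working it through.** **Step 1. The plan's own figure.** 6 sessions per week × 2 weeks = 12 sessions, as the Acupuncture group section states.

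**Step 2. Contacts fixed by the protocol after baseline.** The baseline evaluation precedes treatment, so it cannot pick up on-treatment events. What remains is 12 sessions + 1 week-2 evaluation = 13 in the acupuncture arm and 1 in the control arm. These are minimum counts. The number of ward contacts is not stated for either arm.

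**Step 3. How far this could move the counts.** The documents give no event rate, reporting probability or screening sensitivity, so the following is an illustration on assumptions. Let

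- p = true risk that a patient has an event, equal in both arms (assumed 0.20 to 0.40);
- q = chance that an event is reported at any one contact, independent across contacts (assumed 0.05 to 0.20);
- s = sensitivity of screening common to both arms (assumed 0 to 0.9);
- c = contacts shared by both arms (1 for the week-2 evaluation alone, or 14 for roughly daily ward contact);
- n = 20 per arm (Sample size section: 16/(1 − 0.20) = 20).

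Probability that an event is recorded:

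- control: 1 − (1 − s)(1 − q)^c
- acupuncture: 1 − (1 − s)(1 − q)^(c + 12)

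Expected patients with a recorded event = n × p × that probability.

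Example with p = 0.40, q = 0.10, s = 0, c = 1. Control: 1 − 0.90 = 0.10, and 20 × 0.40 × 0.10 = 0.8 patients. Acupuncture: 1 − 0.90^13 = 0.746, and 20 × 0.40 × 0.746 = 6.0 patients. The true number is 20 × 0.40 = 8 in each arm.

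For p = 0.40 and q = 0.10:

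| Setting | Recorded, control | Recorded, acupuncture | Expected patients of 20, control vs acupuncture | Chance of two-sided Fisher p < 0.05 |
|---|---|---|---|---|
| c = 1, s = 0 | 10.0% | 74.6% | 0.8 vs 6.0 | 49.5% |
| c = 1, s = 0.5 | 55.0% | 87.3% | 4.4 vs 7.0 | 8.8% |
| c = 1, s = 0.9 | 91.0% | 97.5% | 7.3 vs 7.8 | 2.7% |
| c = 14, s = 0 | 77.1% | 93.5% | 6.2 vs 7.5 | 3.9% |

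The first row with p = 0.20 gives 0.4 versus 3.0 patients and a rejection chance of 11.8%. The protocol plans no Fisher test. The last column only shows how often the imbalance would look convincing if someone applied one.

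**Step 4. Range.** Over the whole grid, the acupuncture-minus-control difference in expected recorded patients runs from 0.02 (p = 0.20, q = 0.20, s = 0.9, c = 14: 3.999 − 3.982) to 5.96 (p = 0.40, q = 0.20, s = 0, c = 1: 7.56 − 1.60). The largest gaps need few shared contacts and no common screening. With either frequent shared contact or sensitive common screening, most of the gap goes.

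**The case against.** Much can fairly be said on the other side.

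- **Voluntary report is not the only route.** A reader who stops at the first half of the sentence might infer that it is. The second half provides for examination and laboratory tests in either arm. This stands. What remains is that the second route is optional and unscheduled.
- **The control arm's contacts are unknown.** A reader might infer that controls are seen only at the two evaluations. The documents do not say so. Both arms receive individualised basic medication soon after a stroke, and usual care may bring frequent contact. This stands too. However, the adverse events section does not tie enquiry to those contacts.
- **No between-arm safety analysis is stated.** The article commits only to observing and recording events. The chi-square sentence follows one about baseline material and does not name adverse events. It would therefore be wrong to say that a planned safety comparison is biased, or that safety is a formal second objective. The point reaches only as far as any by-arm listing that readers will compare.
- **Detail may sit elsewhere.** A full protocol or case report form could hold a schedule of enquiry, and its absence from an article is no fault. But the article does state a method, in optional terms, and that stated method is what should change.
- **Blinded assessment.** Under Outcome measures, "All outcomes will be measured by evaluators who will be blinded to group allocation". If this covers adverse events, it protects how they are judged. It does not equalise which events come to notice.

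**Conclusion.** The point holds as a minor one on safety reporting. As written, adverse events are found by two optional routes without common timing, while one arm has 12 additional sessions and no matching contact is described in the other. By-arm counts may therefore be biased by opportunity to report.

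The size cannot be derived from the documents. The range of about 0 to about 6 patients of 20 rests wholly on the assumed event risk, reporting probability, screening sensitivity and number of shared contacts. The lower end applies if controls have frequent ward contact or both arms are screened alike.

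Two stronger readings are not supported. One is that the counts can say nothing about safety in either direction: in several plausible settings the distortion is slight, and some excess under acupuncture would be real because needling events can occur only there. The other is that the primary MRI outcome is affected. Removed criteria does take out patients with serious adverse reactions, complications or deterioration, so a path through unequal detection can be imagined. Serious events should be noticed in either arm, however, and nothing in the documents shows such an effect.

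**What to change.** In Adverse events and safety monitoring, replace the optional wording with one short adverse event checklist, asked of every patient in both arms on the same pre-set days, for example mid-treatment and week 2. Then state how the results will be presented:

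- the events found by this common enquiry form the main by-arm summary;
- all events found by examination, laboratory tests or spontaneous report are still reported, so that nothing is discarded;
- events noticed at needling sessions are listed separately as acupuncture-procedure events;
- the by-arm contrast is descriptive.

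The cost is a short protocol change, a one-page checklist and one brief extra enquiry per patient by existing staff. Treatment does not change. It should be settled before data collection where possible, because events missed during treatment cannot be fully recovered at analysis.

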### Data collection and statistical analysis

Data will be collected using the paper CRFs which will be kept in a locked cabinet at the end of the trial. Statistical analysis of data will be performed by an independent researcher. For dislocated subjects, we will record the number and reason for termination, especially adverse events. Data will be analyzed using the R software version R-4.2.2. Statistical significance is defined as a *p* value of <0.05.

For comparisons of baseline material, measurements that follow a normal distribution overall will be expressed as mean ± standard deviation (
$\bar{X}$
 ± SD), and the whole data that do not follow a normal distribution will be expressed as median (interquartile range, IQR) [M (P25-P75)]. Count data will be expressed as the number of cases (n) and percentage (%) using the X^2^ test. The *t*-test or Mann–Whitney U-test will be chosen to compare the two groups’ scores on each scale based on a normal distribution and homogeneous variance. For within-group comparisons, changes in scores will be assessed by paired *t*-test or Wilcoxon rank-sum test. For subjects who discontinued or deviated from the intervention, listwise deletion or multiple interpolation will be used.

The multimodal MRI images will be analyzed by MATLAB 2023a and the statistical parameter graph software Statistical Parametric Mapping (SPM)12. Before data processing, all data will be removed the first 10 time points to retain the stabilized images; and adjust for differences arising from the time points, after which orientation alignment will be performed; and all aligned functional images will be aligned to the montreal neurological institute (MNI) space with a voxel standard size of 3 mm × 3 mm × 3 mm, and then the functional images will be smoothed with a Gaussian kernel of 6 mm × 6 mm × 6 mm. Afterward, the images will be datamined by extracting the indicators. Data will be analyzed with two independent samples *t*-tests to compare the differences between the patient group before treatment and the healthy group, as well as the differences between the acupuncture group and the no-acupuncture group after treatment. The longitudinal changes in MRI indexes before and after the respective treatments of the two groups of patients will be observed with paired *t*-tests. Age, gender, BMI, blood pressure, and history of diabetes will be used as covariates in data analysis.

Finally, the statistically significant MRI index values of the acupuncture group will be extracted and analyzed by Pearson correlation with the clinical scores of this group before and after treatment.

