**Methods and analysis:**

This trial is a randomized controlled trial. Patients who meet the criteria will be recruited and randomly divided into 2 groups. One group will receive acupuncture treatment and another group will not receive acupuncture treatment. Both groups will receive conventional treatment. In addition, 20 healthy individuals will be recruited who will not receive any treatment. The total course of treatment is 14 days. The primary outcome is multimodal MRI analysis. For safety assessment, adverse events will be observed and recorded.

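### Seven MRI indices are listed as primary, with no index, region or contrast designated and no stated adjustment across indices at p<0.05

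*Protocol article*

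**What the plan says.** All references are to the protocol article.

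- **Abstract, Methods and analysis:** "The primary outcome is multimodal MRI analysis". This names a technique rather than an endpoint.
- **Primary outcomes:** the section describes measures and ranks none of them. On BOLD-fMRI it says "Amplitude of low frequency fluctuation (ALFF) and regional homogeneity (ReHo) are common evaluation indicators", adds that for ALFF "its derivative, fraction amplitude of low frequency fluctuation (fALFF), can better remove noise signals", and continues with "Functional connectivity (FC) reflects functional integration between regions". For structural images, "gray matter volume or gray matter density can be obtained by calculating the gray matter". It then adds FA from DTI and CBF from ASL. Counting fALFF separately and grey matter once gives seven.
- **Data collection and statistical analysis:** the general threshold is "Statistical significance is defined as a *p* value of <0.05". The MRI paragraph sets four families of t-tests: patients before treatment against healthy people, acupuncture against non-acupuncture after treatment, and a paired before-after test in each patient arm. None is called the primary test. No adjustment across indices or within maps is mentioned.
- **Same section, last sentence:** "the statistically significant MRI index values of the acupuncture group will be extracted" and correlated with that group's clinical scores.
- **Sample size:** the section relies on a cited result for a 0.05 threshold at single-voxel level, takes 16 per group and inflates this to 20.

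**The concern.** A primary outcome should fix, before results are known, which single test (or which adjusted set of tests) decides whether the trial has shown what it set out to show. Here any of seven indices, in any region and in any of four contrasts, could be reported as the primary finding, each at 0.05.

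Two features add to the problem. Patients enter within two weeks of stroke with infarcts 3 to 5 cm across, so differences from healthy people, and change over two weeks within an arm, are to be expected whatever acupuncture does. Unless the randomised contrast is named, those results could also be presented as a positive primary outcome. In addition, the closing correlation step carries forward only values that reached significance in the acupuncture arm, so a chance finding would be selected and then given a clinical interpretation.

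The Discussion expects the results to support wider clinical use of the method. That purpose needs a primary test whose error rate is known.

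**Working it through.** **The plan's own figure.** The article states no familywise error rate. Its only checkable figure here is the dropout inflation: 16 / (1 − 0.20) = 20 per group, which reproduces. The 16 is a literature convention given without effect size or SD, so it cannot be derived.

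**Inputs from the article.** Seven indices (Primary outcomes); alpha 0.05 and four sets of MRI t-tests (Data collection and statistical analysis); 16 per group planned, 20 enrolled (Sample size); 3 mm voxels and a 6 mm smoothing kernel for functional images (statistical section).

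**Step 1: randomised contrast, one test per index, independent.** Chance of at least one false positive = 1 − 0.95^k.

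| Count of indices | k | Result |
|---|---|---|
| fALFF folded into ALFF | 6 | 26.5% |
| As listed | 7 | 30.2% |
| Grey-matter volume and density both used | 8 | 33.7% |

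**Step 2: allow for correlation.** Several indices come from the same BOLD series, so independence is an upper case. With seven equicorrelated normal test statistics (400,000 draws, two-sided 0.05):

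| Correlation | At least one false positive |
|---|---|
| 0 | 30% |
| 0.3 | 27% |
| 0.5 | 23% |
| 0.8 | 15% |

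The correlations are assumptions; the article gives none. Over this range the error rate is three to six times the nominal 5%.

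**Step 3: all four sets of tests.** 7 × 4 = 28 tests, and 1 − 0.95^28 = 76.2% under independence and a null everywhere. The objection below explains why this is not the figure to rely on.

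**Step 4: conditional on uncorrected voxelwise maps.** At 0.05 each, 59 effective independent tests already give 95%. Assuming a brain volume of 1.0 to 1.5 L, a 3 mm grid (27 mm³ per voxel) holds about 37,000 to 56,000 voxels. In simulated null maps (36 × 36 × 36 = 46,656 voxels, 6 mm smoothing), every map contained voxels below 0.05: 60 of 60 at 16 per arm and 40 of 40 at 20 per arm, on average about 2,300 voxels, or 5%.

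**Step 5: after the fix.** One named test: 5.0%. Bonferroni over seven: 0.05 / 7 = 0.00714 each, familywise 1 − (1 − 0.00714)^7 = 4.9%. Holm begins at the same 0.00714 and also keeps the familywise rate at or below 5%.

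**Step 6: power cost.** With 16 per arm and 80% power, a two-sample t-test detects a standardised difference of about 1.02 at 0.05, and about 1.33 at 0.05/7.

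**The case against.** The strongest reply is that no correction has been ruled out. The p<0.05 sentence follows the one on R and is general, while the MRI analysis has its own paragraph under SPM12. A significance level of 0.05 is compatible with a corrected 0.05, and map thresholds are a setting that an article may leave to a fuller plan. This stands. A reader might infer that a positive primary result is close to guaranteed, or that the trial cannot fail, but the article does not support that. It never says that maps will be read uncorrected, and the single-voxel 0.05 in Sample size describes a cited power result, not this trial's decision rule. That figure, with SPM12, normalisation, smoothing and the lack of any named region, makes the uncorrected reading plausible and no more.

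A reader might also quote the 76%. That pools the randomised contrast with a patient-healthy comparison and two within-arm comparisons in which real differences are likely, so a null across all 28 tests is not credible. Only the arm-versus-arm comparison bears on a treatment effect.

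Nor should seven whole-brain maps be assumed. FC is described as between regions, the 3 mm grid is stated for functional images only, and grey-matter and FA analyses cover parts of the brain. The voxel count in Step 4 therefore cannot be applied to every index.

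The study can also be described as mechanistic, with clinical scales secondary. That moderates the stakes, but it does not explain why an outcome labelled primary is left open. Choosing the primary variable belongs in the protocol, and here the protocol addresses the matter and leaves seven candidates.

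**Conclusion.** The concern holds in a limited form. Seven indices are listed as primary, none is designated, no region or contrast is designated, and one p<0.05 rule is given with no stated adjustment across indices. For the randomised week-2 contrast, with one test per index, the chance of at least one false-positive index is about 30% under independence and about 15% to 27% for assumed correlations of 0.8 down to 0.3. A figure near 100% applies only on the condition that voxelwise maps are read at an uncorrected 0.05. The missing primary designation is certain from the text; the uncorrected reading is inferred from silence. The designation should be settled before any group results are seen, because it cannot be repaired credibly afterwards.

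**What to change.** By amendment, before group results are seen:

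1. Name one primary index in one predefined region or mask, tested on acupuncture versus non-acupuncture after treatment at two-sided 0.05. The choice is the sponsor's. Motor-area FC is one option, since the Discussion cites an effect on it in healthy people for the same PC6-DU26-SP6 combination. The bilateral M1 result cited there concerns GB34, which is not among this trial's points, and is weaker support.
2. If no single index can be chosen, apply Holm across the seven for that contrast, with one p value per index (from a predefined region, or corrected over the map).
3. Label the remaining indices, the patient-healthy contrast, the within-arm paired tests and the closing correlations as secondary or exploratory.
4. State that p<0.05 on any voxelwise map means family-wise-error-corrected at voxel or cluster level.
5. Restate the sample-size justification to match the chosen test, since it now rests on a 0.05 threshold at single-voxel level.

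**Cost.** An amendment and settings available in SPM12; no new scans or visits. Fewer regions will be nominally significant and power falls at 16 to 20 per group. Under option 2 at 16 per arm, the difference detectable with 80% power at Holm's first step rises from about 1.02 to about 1.33 SD. Option 1 avoids the loss from adjusting across indices.

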### Sample size

This study focuses on MRI data. The sample size was calculated based on similar previous studies. Through reading the research literature on the mechanism of the functional effects of acupuncture on the brain, we found that the acute phase of stroke is generally characterized by an acute condition and poor compliance. Desmond et al. (8) showed that when analyzing functional MRI data with a free threshold of 0.05, it is probably necessary to include at least 12 subjects to achieve an activation efficacy of 80% or more at the single voxel level. Anecdotal evidence (9) suggests that fMRI studies typically involve 12 to 16 subjects per group. Therefore, we included 16 subjects in each group. Considering the high dropout rate, we set the 20% dropout rate and finally included 20 subjects per group. So, a total of 40 CIS patients and 20 healthy people will be enrolled.

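### The non-parametric test named for before-after changes in scale scores is the rank-sum test, which is for independent samples; paired data need the signed-rank test

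*Protocol article*

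**What the plan says.** The NIHSS, mRS, FMA, MBI and EQ-5D "will be assessed before and after 2 weeks of treatment as secondary outcomes" (Secondary outcomes), and "Patients in both groups will be evaluated at baseline and week 2" (Outcome measures). Each patient therefore contributes two scores per scale.

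Data collection and statistical analysis assigns tests to these scores in two consecutive sentences:

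- Between groups: a t-test, or the "Mann–Whitney U-test will be chosen to compare the two groups’ scores on each scale".
- Within groups: "For within-group comparisons, changes in scores will be assessed by paired *t*-test or Wilcoxon rank-sum test".

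The same section keeps to paired tests for the imaging data: changes "before and after the respective treatments of the two groups of patients will be observed with paired *t*-tests". The signed-rank test is not named anywhere in the article.

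**The concern.** Wilcoxon rank-sum and Mann-Whitney U are two names for one procedure, and it compares two independent samples. As written, the plan uses that procedure both for the comparison of the two arms, where it fits, and for baseline against week 2 in the same patients, where it does not. Within one arm the only two samples that it could compare are the baseline scores and the week-2 scores, so the link between a patient's two values is discarded.

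This is not a detail left to a separate analysis plan. The article commits to a specific test, and that test does not match the data.

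The fallback is likely to be used. The mRS has 7 grades, and with 16 to 20 patients per arm some of the scales may well fail a normality condition. What is at stake is a misstated significance level and loss of power for within-arm change.

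**Working it through.** **Inputs from the Protocol article**

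- Evaluable patients per arm: "Therefore, we included 16 subjects in each group" (Sample size).
- Enrolled patients per arm: "we set the 20% dropout rate and finally included 20 subjects per group". Check: 16 / (1 − 0.20) = 20, which reproduces the stated figure.
- Significance level: "Statistical significance is defined as a *p* value of <0.05". Sidedness is not stated; two-sided is assumed.

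**Assumptions not in the document**

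- Before-after correlation ρ, varied.
- A shift of 0.5 SD for the power figures.
- Equal variances and bivariate normal scores.

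**Why the level goes wrong.** For a patient's two scores with common variance σ², the variance of the difference is 2σ²(1 − ρ). A test that treats the samples as independent in effect works with 2σ². At ρ = 0.7 the true variance is 2σ² × 0.3 = 0.6σ². The independent-samples reference is thus too wide by a factor of 2 / 0.6 = 3.3, and p-values come out too large. The rank test follows the same logic on ranks.

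**Simulation.** 20,000 replicates per setting. The rank-sum test (large-sample approximation) was applied to baseline against week 2, and the exact signed-rank test to the differences. Entries are rejection rates at 5%.

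| Pairs | ρ | Type I error, rank-sum | Type I error, signed-rank | Power, rank-sum | Power, signed-rank |
|---|---|---|---|---|---|
| 16 | 0 | 4.5% | 4.4% | 26% | 23% |
| 16 | 0.3 | 2.0% | 4.5% | 23% | 32% |
| 16 | 0.5 | 0.9% | 4.4% | 20% | 43% |
| 16 | 0.7 | 0.15% | 4.4% | 16% | 63% |
| 16 | 0.9 | 0.0% | 4.3% | 11% | 98% |
| 20 | 0.5 | 0.8% | 4.7% | 27% | 55% |
| 20 | 0.7 | 0.15% | 4.9% | 24% | 77% |
| 20 | 0.9 | 0.0% | 4.5% | 20% | 99.6% |

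The rank-sum test is close to its nominal level only when ρ is about zero. If ρ were negative the error would go the other way: at ρ = −0.3 the type I error is 7.8% with 16 pairs and 8.5% with 20. For the same scale in the same patient two weeks apart, positive correlation is the case to expect.

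**Ordinal data.** Because the fallback is meant for scores that are not normal, a further run with 16 pairs used coarse five-level ordinal scores with many ties. Rank-sum type I error was about 0.4%, and power about 14% against 54% for signed-rank. The pattern is the same.

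**The case against.** The strongest reply is that this is a slip of naming. The sentence concerns within-group change, pairs the test with the paired t-test, and uses a different name from the Mann-Whitney test in the sentence before; the MRI analysis also respects pairing. The authors may well have meant signed-rank. That is plausible, but a reader cannot confirm it. An analyst who follows the text in R would get the rank-sum test without warning, because wilcox.test treats samples as independent unless paired=TRUE is set. An analyst who corrects it silently departs from the published protocol.

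The second reply concerns scope, and it stands. Only the non-parametric fallback for within-arm change in secondary scales is affected. The primary MRI outcomes, the between-arm scale comparisons, the sample size and the planned Pearson correlations are untouched. Within-arm tests do not estimate the effect of acupuncture in a randomised comparison. With positive correlation the error is also conservative: it hides change and does not create false positives.

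The third reply is that normal data do not represent the scores sent to this branch, and that the correlation and shift are assumed. It is right that the figures are illustrative and cannot be read as the power for the mRS or NIHSS in this trial. The ordinal run shows, however, that the direction and rough size do not depend on normality.

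**Conclusion.** The point holds: the plan names an independent-samples test for paired data. With 16 pairs and an assumed correlation of 0.5 to 0.9, the nominal 5% test operates at 0.9% or less. Its power for an assumed 0.5 SD shift falls from 43–98% with signed-rank to 20–11%. The direction is certain for any positive correlation; the exact size depends on the assumed correlation, shift and score distribution. Since the consequence is limited to supporting within-arm results on secondary scales, this should be corrected before analysis but does not threaten the trial's main comparison.

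**What to change.** In Data collection and statistical analysis, replace the Wilcoxon rank-sum test with the Wilcoxon signed-rank test for within-group comparisons, leaving the Mann-Whitney U-test for the between-group comparison. In R, call wilcox.test with paired=TRUE. Carry the same wording into any separate analysis plan. The change is one term in one sentence; it needs no new data, no additional patients and no change to the design.
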